#### Training of research assistants

This study will unify the training to guide research assistants in their research work. Research assistants will master the standard operation of the microcurrent stimulation device, strictly follow the standard operating procedure, and minimize the error caused by the implementation process. For the Medical Examination Center and other related departments involved in the study, we have established a standard operating procedure, and a specific research assistant will be in charge of an item.

## Discussion

RP is a hereditary neurodegeneration of the retina. Multidisciplinary integration plays a positive role in promoting the treatment of this disease. A number of trials have been performed to develop an effective therapy to control the progression and complications of RP, including restoring defective genes and stem cell transplantation.

ES has been confirmed as a promising physical therapy which may recover visual functions in patients suffering from various ophthalmopathy, such as dry eye, glaucoma, traumatic optic neuropathy, retinal vein occlusion, RP, macular degeneration, and other eye diseases. The study demonstrated that transcorneal electrical stimulation (TcES) improved visual function of RP model in animal experiments, which was closely associated with the survival of the retinal ganglion cells and photoreceptors. Even more, the study showed that TcES was operated in clinical trials. However, TcES may lead to AEs, such as dry eye and foreign body sensation, whereupon Miura applied transdermal electrical stimulation therapy around the eyes and forehead and demonstrated the efficacy and safety without any adverse reactions of the cornea, skin, or facial nerve [23]. In order to balance the pros and cons, we bring forth new ideas for the therapy and decide to use TpES. Electricity deliveries to the eyes are via electrodes attached to the eyelids of subjects, without contacting with the cornea and conjunctiva. Compared with TcES, TpES has no side effects such as dry eye, punctate keratitis, and the risk of infection caused by the operation. Additionally, the device shows a non-invasive approach that can be performed by patients themselves. Based on clinical experience, TpES have proven to be effective and safe in Norway and other countries [24]. In our study, the four modulation frequencies are pre-set in the device. In general, it has been shown that a stimulation frequency of 20 Hz is ideal for stimulation. However, the optimal frequency for the use of retinal electrical stimulation has not been clearly established. Further research conducting varying stimulation frequency is needed with the potential to improve treatment methods for the treatment of ES.

Generally speaking, N-of-1 trial is a double-blind, randomized, multi-crossover trial with a single case as a control to evaluate the efficacy of the two therapies. N-of-1 trial belongs to RCT. In clinical practice, clinicians and patients pay more attention to the changes of curative effect after individuals taking medicine. This leads to RCT-based population evidence that may not be appropriate for individualized patients. Therefore, the research method for individual patient’s curative effect evaluation is indispensable. That is why N-of-1 came into being.

The clinical research is the first application in RP patients with the TpES therapy. With respect to the rationale for carrying out N-of-1 trial rather than RCT, we take the following reasons into consideration.N-of-1 trials are randomized, prospective, controlled, multiple crossover trials in a single patient. Such trials are suitable for the following clinical applications: (1) chronic disease; (2) experimental treatments for rare diseases or with little or no previous research; (3) doubtful about the efficacy and safety of interventions for certain diseases; (4) the intervention has the characteristics of quick onset and short half-life period and the effect can disappear quickly after the intervention is stopped.RP comprises a group of inherited retinal degenerative diseases with a prevalence of 1 in 4000, affecting 2 million persons globally. RP is associated with 3000 mutations in 100 genes. As a rare and chronic disease, adequate recruitment for group trials is not always feasible, informed consent is difficult to obtain, and retention is difficult too. Compared with RCT, the N-of-1 trial has higher power and requires smaller sample sizes.RP is a highly heterogeneous disease. Studies have shown that genotype plays an important role in RP progression. Besides it, there are many other risk factors that may have effect on the progression of RP, such as inheritance patterns, smoking, physical activity, and other demographic and environmental factors. Due to the small cohort sample size and the large clinical heterogeneity of RP patients, it is difficult to obtain high-quality evidence of therapeutic effectiveness. With the consideration of heterogeneity, N-of-1 trial is a more suitable choice.There have been no reports of transpalpebral electrical stimulation for RP treatment up to now. It is an individualized treatment, and the intensity of stimulating current varies with the condition of the retinopathy in each patient. In the trial, patients will perform the treatment by themselves. Therefore, N-of-1 trial has better feasibility than conventional RCT. Moreover, the intervention has the characteristics of quick onset, and the effect can disappear relatively quickly after the intervention is stopped, which make it suitable for N-of-1 trial.

Taken together, based on the characteristics of RP and the intervention method, it is very suitable for the study of RP.

This trial has two strengths. First, RP is a rare clinical eye disease with a low prevalence. The patients are required to undergo three cycles of crossover trial, so the sample size included in this study is small. N-of-1 trial is precisely suitable for studying RP. Second, the research method of N-of-1 trial is relatively flexible. During each cycle, the effect of treatment can be directly evaluated by observing and comparing patients in two periods. There is no necessity to wait until the end of the trial to make a statistical analysis of relevant data.

A limitation of the trial is that it requires multiple periods of observation. Therefore, the trial usually last longer than common RCTs.

The lack of long-term benefits of patients is another potential limitation. It is known that RP is a chronic and progressive eye disease. Our study protocol does not carry out the follow-up period, and the follow-up effect of patients cannot be observed.

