### Study design

This is a prospective, comparative, and single-blind N-of-1 trial, which includes 3 crossover comparisons. Each comparison includes an 8-week treatment period (A) and an 8-week control period (B). According to the random number generated by Strategic Applications Software (SAS), the random arrangement of AB or BA is presented in each cycle (Fig. 1).

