### Sample size

The sample size was calculated from SUN’s previous study [16]. The primary outcome was the change of mean defect (MD) value of VF after 8 weeks of treatment compared with baseline. Based on the reference (Sun et al.), the MD value of the treatment group is 2.06 ± 1.73. The MD value of the control group is 0.73 ± 1.93. The difference between the effect values of the treatment period and the control period was 1.43, and the standard deviation of the two periods was 1.93. When a two-tailed test with a test power of 80% and significance level of 5% was applied to the research, 10 cases were calculated [17]. Taking into account of 20% dropout rate, we ultimately identified 12 participants.

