#### Primary outcome

In this study, the primary outcome is VF [18]. Quantitative index of VF, including MD, mean sensitivity (MS), and square root of loss variance (sLV), will be examined by OCTOPUS automatic perimetry. The 32-test procedure is suitable for visual acuity greater than 0.3, and the LVC test procedure is suitable for visual acuity less than 0.3. The examination time points are before treatment and then at week 8, week 16, week 24, week 32, week 40, and week 48 (Table 1).

**Table 1 Tab1:** Schedule of enrolment, intervention, assessment

Item	Screening	Observation period						
		Cycle 1		Cycle 2		Cycle 3		Closeout
Time point	Enrollment	Weeks 1–8	Weeks 9–16	Weeks 17–24	Weeks 25–32	Weeks 33–40	Weeks 41–48	
Demographic data	√							
Medical history	√							
Informed consent form	√							
BCVA	√	√	√	√	√	√	√	
VF	√	√	√	√	√	√	√	
OCT	√	√	√	√	√	√	√	
FAF	√	√	√	√	√	√	√	
ERG	√	√	√	√	√	√	√	
NEI VFQ-25	√	√	√	√	√	√	√	
Adverse event		√	√	√	√	√	√	

√ Items that must be performed

*BCVA* Best corrected visual acuity, *VF* Visual field, *OCT* Optical coherence tomography, *FAF* Fundus autofluorescence, *ERG* Electroretinogram, *NEI VFQ-25* 25-Item National Eye Institute Visual Function questionnaire

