### Safety evaluation

A standard examination will be performed to evaluate treatment safety at the beginning and the end of each period. The most common minor adverse events (AEs) from the ES procedures are skin allergies, headache, and dizziness. Other AEs such as unusual or uncomfortable sensations will be reported at the end of daily stimulation sessions.

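### Scheduled adverse-event collection ends at week 48 with no follow-up, so the participants whose last period is stimulation (about half) have no scheduled safety observation after it

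*Protocol article*

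**What the plan says.** All references are to the protocol article.

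- **Objectives:** the aim covers safety as well as efficacy.
- **Study design:** there are three cycles, each with 8 weeks of stimulation (A) and 8 weeks of control (B), and "the random arrangement of AB or BA is presented in each cycle".
- **Primary outcome, Table 1:** a tick marks "Items that must be performed". The adverse-event row is ticked in the six blocks from weeks 1–8 to weeks 41–48. The table has a Closeout column, but it carries no time point and no tick in any row.
- **Primary outcome, text:** "The examination time points are before treatment and then at week 8, week 16, week 24, week 32, week 40, and week 48". The list stops at the end of the last period.
- **Safety evaluation:** "A standard examination will be performed to evaluate treatment safety at the beginning and the end of each period". Other events, such as unusual sensations, are reported at the daily sessions. The common minor events named are skin allergies, headache and dizziness.
- **Discussion, limitations:** "Our study protocol does not carry out the follow-up period, and the follow-up effect of patients cannot be observed". The paragraph presents this as a loss of information on long-term benefit and does not mention safety.

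**The concern.** A treatment period in weeks 41–48 is handled differently from every earlier one. After an earlier stimulation period the participant stays in the trial, and adverse events continue to be recorded for at least one further 8-week block. After a final stimulation period, scheduled observation ends with the stimulation itself, apart from the examination that closes the period. Who falls into this group is decided by the order drawn for cycle 3.

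Two kinds of information are at stake: events that begin after the last stimulation session, and the outcome of events that are open at week 48. Any loss of this kind can only make the safety record look cleaner. The Discussion calls this the first use of this therapy in patients with retinitis pigmentosa, and participants set the current themselves, so the safety record matters. Recruitment is planned from January 2023 to March 2024 and participation lasts 48 weeks. The first finishers would leave around December 2023 while others are still on treatment, some until about early 2025. Late information from early finishers could therefore still be useful to the trial.

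**Working it through.** The article gives no figure for the share of participants who end on stimulation, so there is none to reproduce. The inputs are 12 participants (Sample size: "Taking into account of 20% dropout rate, we ultimately identified 12 participants"), three cycles of two 8-week periods (Study design), and adverse-event recording to week 48 (Table 1). I assume that order is 1:1 and independent between cycles and participants. The article says only that it is random.

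**Step 1. Recorded time after each treatment period.** This is 48 minus the week in which the period ends.

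| Cycle and order | Treatment ends at week | Recorded weeks afterwards |
|---|---|---|
| 1, AB | 8 | 40 |
| 1, BA | 16 | 32 |
| 2, AB | 24 | 24 |
| 2, BA | 32 | 16 |
| 3, AB | 40 | 8 |
| 3, BA | 48 | 0 |

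Only a cycle 3 in the order BA leaves no recorded time after treatment.

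**Step 2. The eight equally likely sequences.** These are ABABAB, ABABBA, ABBAAB, ABBABA, BAABAB, BAABBA, BABAAB and BABABA. Four of the eight end in A, so the probability of finishing on stimulation is 4/8 = 0.5.

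**Step 3. Number of participants.**
- For n = 12: expected 12 × 0.5 = 6, with 2.5% and 97.5% binomial quantiles of 3 and 9.
- If only 10 complete: expected 10 × 0.5 = 5, with quantiles of 2 and 8.

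**Step 4. What follows each treatment period.** The eight sequences contain 8 × 3 = 24 treatment periods.
- 4 of 24 (1 in 6) fall in weeks 41–48 and are followed by nothing scheduled.
- 16 of 24 are followed directly by a control period.
- 4 of 24 are followed directly by another stimulation period (a BA cycle, then an AB cycle).

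So 20 of 24 are followed by at least 8 recorded weeks, and in 4 of those 20 the next block is itself stimulation. With 12 participants there are 12 × 3 = 36 treatment periods, of which 36 × 1/6 = 6 are expected to have no recorded time afterwards.

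**Step 5. What the week-48 examination covers.** A safety examination falls at the end of each period, including the last. An event present then can be recorded. Its later course, and any event that starts afterwards, have no scheduled collection point.

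**The case against.** The strongest reply is that little is likely to be lost. An examination closes the last period, and events are reported at the daily sessions before it. The events named are minor and linked to the procedure, and the Discussion describes an intervention whose effect fades relatively quickly once stopped. The article cites no delayed harm. Every participant, whatever the order, also contributes two earlier treatment periods with later recording. All of this stands, and it limits the size of the point. It does not remove the point, because fading of benefit is a premise about efficacy and does not settle how long adverse events should be watched.

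A second reply is that post-treatment reporting is a detail for the full protocol, and that the Discussion sentence concerns follow-up of effect. The sentence is indeed about effect. Table 1 and the Safety evaluation section carry the safety point more directly. But the article states outright that there is no follow-up period, and its assessment dates end at week 48. This is a stated design feature and not an omitted detail.

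Stronger readings are tempting and are not supported:
- A reader might infer that events persisting after the last session are never recorded. The end-of-period examination contradicts this. Only their outcome is lost.
- A reader might infer that a serious late event could not reach the rule under Termination criteria. Nothing bars a spontaneous report, and the trial holds telephone and WeChat details. What is missing is a scheduled contact.
- A reader might treat all earlier periods as having a clean off-treatment window. In 4 of 20 the next block is more stimulation.

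**Conclusion.** The point holds as a modest gap in safety ascertainment. Under an assumed 1:1 order, about half of participants (6 of 12 expected, range 3 to 9), and so about 1 in 6 treatment periods, have no scheduled safety observation after stimulation ends beyond the examination at about week 48. All other treatment periods have at least 8 further recorded weeks. The difference follows from the order of the last cycle.

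These counts describe sequences and not missed events. It is nearly certain that someone will end on stimulation, but that does not show that any event will be missed. The article gives no event rate or onset delay from which a loss or bias could be estimated. The efficacy result is unaffected. This is a cheap improvement to a stated aim, not a flaw that undermines the trial.

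**What to change.** In Table 1, tick adverse events under the existing Closeout column and give the column a time point. Make one telephone or WeChat contact per participant after week 48, at the same interval for everyone whatever the order, using the contact details already held (Management of study participants). Record new events with their onset dates, and the outcome of any event open at week 48. Onset dates allow an event first noted after stimulation to be placed correctly in time. Add to the limitations paragraph in the Discussion that the lack of follow-up also bears on safety.

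The interval is for the investigators to choose. A contact at 8 weeks would match the shortest recorded time after any earlier treatment period. A sooner contact would narrow the gap without closing it.

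The cost is 12 short contacts, one table entry and somewhat longer participation. No treatment, visit or efficacy assessment changes.

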## Trial status

The updated version of trial protocol (version 2.0, 1 December 2022) has been reviewed and approved on 23 December 2022 (YKEC-KT-2022–043-P002). Recruitment is start in January 2023 and is expected to finish in March 2024.

## Data Availability

The datasets analyzed during the current study are available from the corresponding author on reasonable request, as is the full protocol.

## Abbreviations

AEs: Adverse events
BCVA: Best corrected visual acuity
CRF: Case report form
e-CRF: Electronic case report form
ERG: Electroretinogram
ES: Electrical stimulation
FAF: Fundus autofluorescence
MS: Mean sensitivity
MD: Mean defect
OCT: Optical coherence tomography
RP: Retinitis pigmentosa
RPE: Retinal pigment epithelial
SAS: Strategic Applications Software
sLV: Square root of loss variance
SPSS: Statistical Package for the Social Sciences
TcES: Transcorneal electrical stimulation
TpES: Transpalpebral electrical stimulation
VF: Visual field
VRQoL: Vision-related quality of life
